### Ethics

Ethical approval has been granted from the human research ethics committee of Children’s Health Queensland (HREC/19/QCHQ/50464) and the Queensland University of Technology (1900000696). The trial has been prospectively registered with the Australian New Zealand Clinical Trials Registry (ACTRN12619000841178). Before enrolling in the trial, full written and informed consent will be obtained from legal parents/guardians of all participants, verbal assent for children aged seven to 13 years, and verbal and written assent for children aged 14 years or older. Participant data will be managed on a secured electronic database (REDCap) and hardcopy forms stored securely at the research facility.

### Safety and adverse events

A standardized protocol will be used to monitor adverse events that may occur during the face-to-face exercise sessions or home-based program. Adverse events commonly related to participating in physical activity may include, but are not limited to muscle soreness, falls, injury, exacerbation of existing symptoms, or any new or changed health problems since the previous contact. Adverse events will be graded using the Common Terminology Criteria for Adverse Events version 5.0 criteria [82]. Serious adverse events related to the intervention will be reported by the chief investigator to the lead ethics committee. Risk assessments with mitigation strategies will be implemented prior to commencing the home-based program.

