## Methods

### Study design

This study is a single-center randomized controlled trial. Participants will be randomized into the intervention arm (*n* = 24) or usual care (n = 24). The study will be conducted in accordance with the Standard Protocol Items: Recommendations for Interventional Trials (SPIRIT) guidelines [42]. See SPIRIT Checklist in Additional file 1. Assessments for all participants will be conducted at baseline (T1), immediately post-intervention (12-weeks post baseline) (T2), and at 6-month (T3) and 12-month (T4) follow-up. Each assessment involves: 2 days of testing at a clinic visit, assessor-administered or self-administered (age dependent) child questionnaire, self-administered parent questionnaire, and monitoring of physical activity by accelerometer for 7 days. An overview of the study design, the schedule for enrollment and study assessments is shown in Table 1.

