### Therapeutic exercise intervention

Participants randomized to the intervention group will receive weekly individualised, goal-directed exercise therapy delivered face-to-face for 12 weeks, along with an accompanying home-based program. Each face-to-face session will be delivered by a qualified physiotherapist or accredited exercise physiologist (referred to hereafter as therapist), for a 30–60-min duration. The intervention will adhere to accepted exercise prescription guidelines for children and adolescents, comprising physical exercise training (cardiorespiratory and strength-promoting activities) and goal-directed task specific practice [43, 44]. At least half of the face-to-face session will be dedicated to cardiorespiratory-focused activities, with the remaining half dedicated to goal-directed activities. Goals selected will be physical activity- related and may include community recreation, sports, or leisure goals. The structure of the therapeutic exercise program, including the type, intensity and duration, will be individualized according to each participant’s age, goals, interests, functional capacity, presence of treatment-related side-effects and co-morbidities.

To supplement the face-to-face sessions, participants will complete a parent-led, home-based exercise program three times per week, up to 30 min of duration each time. The home-based program will replicate the essential elements of the supervised sessions in relation to activity type, intensity, and duration, and will also reflect the resources available at home. Prior to commencing face-to-face sessions, the therapist will complete a home visit to determine what space, equipment, and resources are available to complete the home-based exercise program safely and effectively. Parents will be given a detailed manual (including pictures and descriptions) for delivering the home-based component and will be encouraged to participate in the activities with their child. Peers and siblings may also be included to promote adherence to the home-based program. The home-based program will be monitored via heart rate monitors. The therapist will complete a follow-up home visit, between week four and week eight of the intervention, to provide an opportunity for participants and parents to ask questions about the home-based program, resolve any difficulties completing the program, and review the current activities.

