### Usual care

Participants randomized to the control group will receive care as usual. Usual care is highly variable for children who are PFBT survivors; however, it is anticipated that most participants will not receive direct therapy services for the duration of the study. Usual care may include any therapy (e.g., physiotherapy, occupational therapy, speech and language therapy) and visits to their treating medical practitioner.

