### Participant characteristics

Upon meeting eligibility criteria and providing written consent, participants will complete a demographic and medical information questionnaire, provided to the parent up to 2 weeks prior to their scheduled baseline assessment. The following medical information will also be extracted from patient medical records by trained staff: definitive date of diagnosis, tumor type and grade, intraventricular shunt placement, extent of surgery, site and dose of radiation therapy, agent and cumulative dose of chemotherapy, hormone therapy, dose and frequency of Botulinum Toxin A (BoNTA), and physical impairment (e.g., ataxic gait, hemiplegia).

At each assessment, the following anthropometric measures will be taken: height (Seca 264 digital stationary stadiometer, Seca, Germany), weight (Seca 703, column scales, Seca, Germany), and waist circumference measured using a stretch resistant tape. Information about each participant’s usual care during the study period will be collected through a semi-structured parent interview.

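### As the article describes it, adverse-event monitoring is tied to exercise that only one arm receives, so falls and injuries could not be compared between arms

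*Protocol article*

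**What the plan says.** All the safety text is in the section Safety and adverse events. It opens by setting the scope: "A standardized protocol will be used to monitor adverse events that may occur during the face-to-face exercise sessions or home-based program". It then gives examples of events that may accompany physical activity: "muscle soreness, falls, injury, exacerbation of existing symptoms, or any new or changed health problems since the previous contact". Grading is by CTCAE version 5.0. On serious events it says: "Serious adverse events related to the intervention will be reported by the chief investigator to the lead ethics committee".

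The section Therapeutic exercise intervention says who has the sessions and the home program: "Participants randomized to the intervention group will receive weekly individualised, goal-directed exercise therapy delivered face-to-face for 12 weeks, along with an accompanying home-based program". The section Usual care says of the other arm: "Participants randomized to the control group will receive care as usual".

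Two kinds of contact are common to both arms. Study design states: "Assessments for all participants will be conducted at baseline (T1), immediately post-intervention (12-weeks post baseline) (T2), and at 6-month (T3) and 12-month (T4) follow-up". The content listed for those assessments is clinic testing, child and parent questionnaires and accelerometry. Participant characteristics adds: "Information about each participant’s usual care during the study period will be collected through a semi-structured parent interview". Neither mentions adverse events, and falls and injuries are not among the primary or secondary outcomes.

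**The concern.** The opening sentence defines monitoring by an exposure that one arm has and the other lacks. That is a stated scope, which differs from a detail left to a longer document.

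It matters because the listed events are not specific to exercise. The Background says these children have weaker legs, poorer balance and poorer motor skill than their peers. Falls and worsening of existing symptoms would therefore be expected at some rate without any program, and the randomized control arm is the natural source of that rate. The Background also says that the safety evidence comes mainly from children with blood cancers and that the authors know of no published randomized trial of therapeutic exercise in this population. The Discussion intends the results to inform practice. If events are counted in one arm only, a reader will see a number of falls with nothing to set it against.

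**Working it through.** There is no stated figure to reproduce, so the first step is to compare the sections.

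**1. Who can contribute events under the stated scope**

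| Element | Intervention | Usual care |
|---|---|---|
| Face-to-face sessions | yes, weekly for 12 weeks | no |
| Home program | yes, three times a week | no |
| Adverse-event enquiry described at T1 to T4 | none | none |
| Parent interview | about usual care received | about usual care received |

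On the opening sentence alone, usual care contributes no events by construction.

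**2. How much time the opening sentence covers.** The maximum is 12 sessions × 1 h + 36 home sessions × 0.5 h = 12 + 18 = 30 h. Twelve weeks contain 12 × 7 × 24 = 2,016 h, so the share is 30/2,016 = 1.5%. The clause about problems since the previous contact covers the time between contacts, which is much wider. It names neither an arm nor a contact schedule and sits within a list of activity-related events. The two sentences therefore describe different monitoring windows.

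**3. What one arm can show.** The article gives no fall or injury rates, so every rate from here on is an assumption.
- If 6 of 24 exercise children fall, the rate is 25%. Against an unmeasured control rate of 25% down to 5%, the excess is 0 to 20 percentage points; against a control rate above 25% it is negative. One-arm data cannot separate these cases.
- If no events occur in 24 children, the one-sided 95% upper bound is 1 − 0.05^(1/24) = 11.7%. That bounds a rate in one arm and says nothing about a difference.

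**4. What collecting in both arms would give (24 vs 24).** Half-width of the 95% confidence interval for a risk difference = 1.96 × √[p₀(1−p₀)/24 + p₁(1−p₁)/24].

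| Control p₀ | Exercise p₁ | Half-width (points) |
|---|---|---|
| 5% | 25% | 1.96 × √(0.2350/24) = 19.4 |
| 10% | 30% | 1.96 × √(0.3000/24) = 21.9 |
| 20% | 20% | 1.96 × √(0.3200/24) = 22.6 |
| 25% | 25% | 1.96 × √(0.3750/24) = 24.5 |
| 20% | 40% | 1.96 × √(0.4000/24) = 25.3 |
| 30% | 30% | 1.96 × √(0.4200/24) = 25.9 |

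Power at two-sided 0.05 (normal approximation, pooled variance under the null) is 16% for 10% vs 20%, 41% for 10% vs 30%, 32% for 20% vs 40% and 68% for 10% vs 40%. The comparison would be free of unequal ascertainment by design, but imprecise.

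**The case against.** The strongest reply is that this is a condensed article. It refers to a standardized protocol that is not shown, and that protocol may ask usual-care families about events. This stands in part. A reader might infer that no adverse events at all are recorded in usual care, but the article does not say so; that is an inference from the stated scope. What remains is that the scope as printed leaves usual care out, so either the monitoring or the sentence needs correcting.

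Second, the clause on problems since the previous contact could take in a fall at school. That also stands: such events cannot be said to be definitely excluded. The clause makes the section ambiguous without extending it to the control arm.

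Third, a reader might infer that every event will look as if exercise caused it. The text does not support that. Events are graded, and serious events related to the intervention are singled out, so relatedness is judged at least for those. The weakness is that it is judged without a concurrent comparator. The serious-event sentence also concerns what goes to the ethics committee, not what is recorded, and is weak evidence about collection.

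Fourth, no safety hypothesis is stated and 24 per arm is small. Both are true. They rule out a formal test and any expectation that the trial would settle whether exercise raises or lowers falls. They do not justify counting events in only one arm of a randomized trial.

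**Conclusion.** The point holds in a limited form. As described, monitoring is anchored to activities that only the intervention arm has, no control-arm enquiry is described, and two sentences of the safety section disagree on the window. If that is what is done, no between-arm estimate of falls, injuries or symptom worsening will be possible. If the full protocol already covers both arms, the article's wording should be corrected to say so.

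The primary and secondary efficacy analyses are untouched. What is lost is a randomized safety description, which cannot be reliably recovered later. Its value is modest: half-widths of about 19 to 26 points, resting on assumed event rates of 5% to 40% and all 24 per arm being assessed. It is worth changing because the change is cheap.

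**What to change.** Reconcile the opening sentence of Safety and adverse events with the clause on problems since the previous contact, and state which arms, contacts and period are covered.

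Put the same structured questions (falls, injury, new or worsened health problems, hospital visits) to both arms at T2, T3 and T4, over the same recall periods. Use a parent questionnaire, or an interviewer who is not one of the blinded outcome assessors, because parents may mention the program. Grade with CTCAE v5.0 and tabulate by randomized arm as the number and proportion of children with an event, with the risk difference and its 95% confidence interval and no formal test.

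Keep the in-session log as a separate intervention-arm listing. Merging it into the comparative table would bring back unequal ascertainment.

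The cost is a slightly longer questionnaire or interview and one table. The article gives no timing for the existing parent interview, so its use at all three visits would need confirming. Recall over several months is imperfect, and families know their allocation, so some differential reporting is possible and should be acknowledged with the results. Treatment, sample size and the primary analysis do not change.

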### Primary outcomes

#### Cardiorespiratory fitness

A continuous ramped exercise test for determination of maximal aerobic capacity will be conducted on an electronically braked pediatric cycle ergometer (Ergoselect 150, Ergoline, Bitz, Germany). Following a 2-min warm-up at an output of 10 watts, power output will increase at a rate of 10 W per minute and cycling cadence will be maintained at 75 rpm (rpm) [45]. The test will continue until pedal cadence drops below 60 rpm for 5 consecutive seconds, at which point power output will be reduced to 10 W for a 5-min recovery. Peak oxygen consumption (Peak *V*O_2_) will be determined using the methods described by Day et al. [46]. Breath-by-breath changes in gas exchange and ventilation will be measured using the MetaMax-3B portable metabolic analyzer (Cortex, Leipzig, Germany). Oxygen consumption (*V*O_2_) will be averaged over five second time windows. This measure has been shown to be reliable among children (ICC = 0.96) [47].

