### Secondary outcomes

#### Cardiorespiratory endurance

The Modified Shuttle Test requires participants to walk/run back and forth along a 10-m course in time with a sound signal recording [54]. Speed for the first minute is set to 1.8 km/hour and increased by 0.61 km/hour every minute thereafter. The test is terminated when participants can no longer follow the pace set by the recording and the last lap successfully completed is recorded [55]. Heart rate and perceived effort using the OMNI scale will be recorded just prior to the test and immediately following test termination [56]. The Modified Shuttle Test has been used in pediatric patients with cystic fibrosis and has been shown to be a reproducible and valid measure of cardiorespiratory endurance [55, 57].

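### As worded, adverse-event monitoring and serious-event reporting are tied to the exercise program and do not reach harm from the trial's own limit tests

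*Protocol article*

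**What the plan says.** The section Safety and adverse events in the protocol article sets two scopes. For monitoring, a standardized protocol is used to "monitor adverse events that may occur during the face-to-face exercise sessions or home-based program". For reporting, "Serious adverse events related to the intervention will be reported by the chief investigator to the lead ethics committee".

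The same section gives an open list of event types that may go with physical activity. The list ends with "or any new or changed health problems since the previous contact". On grading it says "Adverse events will be graded using the Common Terminology Criteria for Adverse Events version 5.0 criteria". It does not say how the cause of an event is assigned.

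Under Study design, all participants in both arms are assessed at T1, T2, T3 and T4, and each assessment involves "2 days of testing at a clinic visit". Two of the tests run to the child's limit:

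- Cycle ramp (Cardiorespiratory fitness): "The test will continue until pedal cadence drops below 60 rpm for 5 consecutive seconds".
- Modified Shuttle Test (Cardiorespiratory endurance): "The test is terminated when participants can no longer follow the pace set by the recording".

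The section Usual care gives the control group no trial exercise sessions and no home program.

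**The concern.** Both scope sentences follow the exercise program, but the program is not the only strenuous thing the trial asks of these children. The tests are research procedures, they are done to the limit of effort, and children in usual care do them as well. The Background describes survivors with low fitness and with deficits in strength and balance. The event types listed in the safety section, such as falls, soreness and injury, are as foreseeable in testing as in training.

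A serious event caused by a cycle or shuttle test would be related to the research but not to the intervention. Under the printed rule it need not go to the ethics committee. The safety summary would also describe the program alone, and collection would differ by arm, so it could not support a comparison of harms between arms. No efficacy result is affected.

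**Working it through.** The plan gives no figure on this point, so there is none to reproduce. The check has two parts: reading the rules against the trial's own procedures, and counting the exposure left outside them.

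**1. Meaning of intervention.** The Abstract and the section on the therapeutic exercise intervention use the word for the 12-week program of weekly sessions plus home exercise. Assessments are described separately, under Study design and the outcome sections. The Abstract places randomization after the baseline assessment, so T1 testing comes before any allocation. T2 follows the program, and T3 and T4 are follow-up visits.

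**2. The rules applied to a serious event.**

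| Where the event is caused | In a named monitoring setting? | Covered by the reporting rule? |
|---|---|---|
| Exercise session or home program | Yes | Yes, if judged related |
| Test at T1, before allocation | No | No; no intervention has started |
| Test at T2 to T4, usual care | No; the arm has no such setting | No; the arm receives no intervention |
| Test at T2 to T4, exercise arm | No | Not if caused by the test |

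**3. Exposure.** Inputs from Study design: 24 + 24 = 48 children and 4 assessments. Inputs from the outcome sections: 2 tests taken to the limit. Assumption: both tests are done at every assessment, because the content of the schedule table is not shown.

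- All children: 48 × 4 × 2 = 384 tests.
- Allocated to usual care: 24 × 4 × 2 = 192 tests.
- Before allocation (T1, both arms): 48 × 2 = 96 of the 384.
- With attrition: Sample size and power allows for up to 20% loss and needs 40 children. If 48 are tested at T1 and 40 at each later visit, the total is 48 × 2 + 40 × 3 × 2 = 96 + 240 = 336.

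For contrast, the settings that are named hold 12 face-to-face sessions and 3 × 12 = 36 home sessions per exercise-arm child, which is 48 each and 24 × 48 = 1,152 in total. None of the 384 tests lies within those settings.

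**4. The clause on health problems since the previous contact.** It stands in a list of event types and does not add a setting. Read generously, it lets a therapist note, at a program contact, a problem that began at an assessment. Program contacts occur only in the exercise arm and only between T1 and T2. On that reading the clause can reach T1 testing in that arm, 24 × 2 = 48 of the 384 tests, and nothing in usual care.

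**The case against.** The strongest reply is that this is a condensed journal article. It points to a standardized monitoring protocol that is not shown. The SPIRIT checklist and the ethics application are not shown either. Event forms, attribution fields and the handling of procedure-related events commonly sit in such documents, and the article nowhere says that test-related events are excluded. This stands to the extent that a reader should not infer that such events have no collection or reporting route. It does not remove the point, because the article does more than stay silent: it prints two scope rules, and both are drawn around the program.

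The word contact might also include trial assessments. T1 to T3 are each followed by another assessment in both arms, and a parent interview collects information on usual care. That is possible but not stated. T4 would still have no later visit, and the reporting rule would be unchanged.

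A reader might go further and infer that soreness or a fall from baseline testing would be counted against the exercise program. The documents do not support this as a main point. The therapist makes a home visit before the sessions begin, so at session one the previous contact is naturally that visit. Reporting an event as related to the intervention already requires a judgment of cause. The claim also needs the clause to be read broadly, while the gap in collection rests on reading the monitoring sentence as printed. What remains is that no attribution rule is given.

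Finally, the treating oncologist must judge each child medically able to complete an exercise program. That lowers the risk but does not decide where an event is recorded or reported.

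**Conclusion.** The point holds as a matter of stated scope. Followed as written, the monitoring sentence and the serious-event rule do not cover events caused by the trial's own assessments. The size is up to 384 planned limit tests, 192 of them in children allocated to usual care, assuming both tests at all four visits and no attrition; about 336 in total if 40 children are tested from T2 on. Usual care has no named monitoring setting, and the exercise arm has a partial route at most.

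The documents give no adverse-event rate for testing, so no number of missed events can be stated. They also do not show that the ethics committee would in fact go uninformed, since the full monitoring protocol may cover testing. The point concerns safety oversight and the safety summary. It does not affect the sample size or the primary analysis. The text should be changed, but the trial does not depend on it.

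**What to change.** In Safety and adverse events:

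- Extend the monitoring sentence so that it names the assessment visits alongside the face-to-face sessions and the home program, and say that it applies to both arms.
- Extend the reporting rule to serious adverse events related to the intervention or to any study procedure.
- Record for each event an onset date and an attribution (assessment procedure, exercise program, or neither), and tabulate test-related events apart from program events. Staff who know the allocation should complete the attribution, so that outcome assessors stay blinded.

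If the standardized monitoring protocol already covers testing, only the two sentences in the article need correcting. Otherwise the cost is a wording change, two fields on the event form, slightly more recording and a few more reported events. Assessors already attend the tests, so no extra visit is needed.
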